**Study design**

Experimental design

This is an interventional study: Double-blind (except for blue-light), Randomized, Crossover, Comparative versus referent countermeasure of sleepiness: coffee (2*200 mg of caffeine) and placebo.

The study is divided into the following periods:

1. **selection period** without treatment between selection and inclusion visits to check the absence of exclusion criteria with questionnaires, polygraphic recording (respiratory sleep disorders and periodic leg movements) and actimetry (sleep efficiency, total sleep time)
2. **acute treatment period**, each volunteer will be randomly allocated to successively and randomly receive either continuous blue light exposure or 2*200 mg of caffeine or placebo of caffeine during night driving with at least 1 week between treatment.

Experimental protocol

SELECTION

Participant will complete the French version of the Basic Nordic Sleep Questionnaire (BNSQ), the self-report symptoms inventory SCL-90R, the chronotype questionnaire of Horne and Ostberg, the Epworth sleepiness scale. They will to have 7 consecutive days monitoring using actimeters and 1 night using polygraph.

INCLUSION

Participants will be screened for eligibility criteria. They will sign informed consent, perform cognitive tests, complete the caffeine sensitivity questionnaire. Blood samples will be collected.

DRIVING SESSION

Each subject, will come at the laboratory at 9:30 PM, and will kept awake until the time of the experimental session.

For each driving session (Blue light, caffeine and placebo of caffeine), all participants will drive 400 km (250 miles) on the same 2-lane highway for 4 hours. After 2 hours of driving (200 km, 125 miles) subjects will take a 15-minutes break. The night-time driving session will start at 1:00 AM and Stop at 5:15 AM. At the beginning, middle and end of the driving, participants will be asked to rate their instantaneous fatigue and sleepiness. After driving, sleep recuperation will be recorded in laboratory during a minimum of 6h. Saliva will be collected before and after the driving session and after sleep recuperation.

The subjects were instructed to maintain a regular sleep-wake schedule and were monitored by actimetry during the 3 days preceding each experimental session and during the 3 days after each experimental session.

**
[figure not shown]
**

C: Coffee

P: Placebo

BL: Blue Light

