**Clinical assessment methods**

EFFICACY

Driving session

Driving conditions will be a straight highway on weekdays with usually light traffic conditions, in fair weather. All drivers will be exposed to the same or very similar conditions. During a training session, participants will be instructed to maintain a constant speed (130 kph [80 mph]), to drive in the center of the lane, and not to cross the painted lines separating the lanes except to pass a slower vehicle.

During the whole experiment, a professional driving instruc­tor will monitor the driving speed. He will be ready to take control of the car (equipped with dual controls) if needed. If a participant could no longer drive during a session, he will drive back to the rest area. The car used for the experiment will be equipped with a video system that calculates the driving ability.

The main outcome measure will be the number of inappropriate line crossings (ILC) identified from the video recordings. This measure was selected because epidemiologic findings have shown that 65% of sleep-related accidents occur after an ILC (Sagberg 1999). Several studies have also shown that impaired daytime alertness induces lateral devia­tions during driving (O'Hanlon and Volkerts 1986; Ramaekers and O'Hanlon 1994; O'Hanlon, Vermeeren et al. 1995) and that sleep-related accidents frequently occur with a single car driving off the road and hitting an obstacle with no reaction from the driver (Pack, Pack et al. 1995; Sagberg 1999). We have also demonstrated that the number of ILCs is affected by sleep deprivation (Philip, Sagaspe et al. 2005; Philip, Sagaspe et al. 2005) and improved by classic countermeasures to sleep loss (Philip, Taillard et al. 2006).

An ILC is recorded when the car cross a lateral highway lane marker, as evidenced by video-recording analysis. Exceptions are overtaking manoeuvres or some other necessary driving action, as recorded by the driving instructor. Driving-instructor and video-recording timelines were synchronized at the beginning of each ses­sion. Deviations related to traffic interference will be excluded so as to concentrate on line crossings related to driver status.

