**Statistical considerations**

Determination of sample size

The sample size calculation (G power software) was done in order to allow demonstrating a slight difference between the 2 countermeasures (coffee and blue light) with a power of 90 % and a type-I error =5% approximately 48 subjects have to be included in the study:

Effect size f = 0.3

α err prob = 0.05

Power (1-β err prob) = 0.9

Total sample size: 48 **(24 young and 24 middle-aged)**

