**Analyses of variables**

Analysis of primary efficacy variable

The results will be analyzed by using negative binomial regres­sion in Stata, version 8.0 (Stata Corp., College Station, Texas), using number of ILC per participant as dependent variables and treatments (Blue light, coffee, or placebo), age or type as determi­nants clustered on participants. We reported comparisons of ILC between treatments as incidence rate ratios (IRR) with 95% confi­dence intervals (CI). Where binomial negative regression are not possible because there are no line crossing, the Wilcoxon non­parametric test will be used.

Analysis of secondary efficacy variables

The standard deviation of the position of the car will be compared by a two-way analysis of variance (ANOVA) (age*treatment, genotype*treatment, hormonal type *treatment, cognitive type*treatment, …).

Subjective sleepiness or subjective fatigue will be compared by a three-way analysis of variance for repeated measurements (rANOVA) (time*age*treatment, time*genotype*treatment, time*hormonal type*treatment, time*cognitive type*treatment, …)

Sleep latency, sleep efficiency or sleep EEG power density will be compared by a three-way analysis of variance for repeated measurements (rANOVA) (time*age*treatment, time*genotype*treatment, time*hormonal type*treatment, time*cognitive type*treatment, …).

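### The protocol foresees drives that stop early but does not say when sleepiness and fatigue are then rated, and the repeated-measures ANOVA in its usual form excludes men with incomplete ratings

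*Protocol*

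**What the plan says.** Three parts of the protocol bear on this point.

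- **Study design, Driving session.** The ratings follow the course of the drive: "At the beginning, middle and end of the driving, participants will be asked to rate their instantaneous fatigue and sleepiness". Timing is given for a full drive: "The night-time driving session will start at 1:00 AM and Stop at 5:15 AM", with a 15-minute break after two hours at the wheel. Each man drives three times, once per condition.
- **Clinical assessment methods, Driving session.** A shortened drive is foreseen: "If a participant could no longer drive during a session, he will drive back to the rest area". Nothing is said about the ratings still due that night.
- **Analyses of variables, secondary efficacy variables.** The method is fixed: "Subjective sleepiness or subjective fatigue will be compared by a three-way analysis of variance for repeated measurements". Time is one factor, with treatment and age (or a genotype, hormonal or cognitive type) as the others. No provision is made for a shortened drive or an incomplete man.

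The primary analysis is a negative binomial regression of line crossings, clustered on participant.

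**The concern.** For a completed drive the three rating times are clear. For a stopped drive the end of driving is whenever the man stopped, and the protocol leaves two readings open.

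- **No further rating is taken.** The man then lacks at least his end rating. A classical repeated-measures ANOVA needs all nine cells and drops him, including his nights driven in full. The clustered count model would keep his other sessions, so the primary and these secondary results could describe different sets of men.
- **The rating is taken at the stop.** It is present but early, and it is entered at the same level of the time factor as ratings made at 5:15 AM. A man who stops before the break still has no middle rating.

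The trial studies driving while acutely sleepy, so inability to continue is plausibly tied to the quantity being rated. The protocol expects both countermeasures to help, so stops are plausibly commonest under placebo. Excluding those men would tend to lower late-night placebo scores and shrink the contrast with coffee and blue light.

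**Working it through.** **Plan's own figure.** The only computed figure is the total of 48 men, from "Effect size f = 0.3", a type-I error of 5% and 90% power. The test family, number of groups, number of measurements and correlation are not stated, so 48 can be neither confirmed nor refuted. A within-subject ANOVA with 3 measurements needs 49 to 50 men at correlation 0 and 25 to 26 at 0.5. A within-between interaction with 6 groups, 3 measurements and correlation 0.5 gives exactly 48. This point does not depend on that calculation and uses 48 only as the denominator. No dropout allowance is shown.

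**Rating times in a full drive.** Start 1:00; 1:00 + 2 h = 3:00; plus 15 min = 3:15; plus 2 h = 5:15. For a purely hypothetical stop at 2:15 AM, a rating at the stop would come 3 h before the planned end rating and before the middle one.

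**Ratings per man.** 3 occasions × 3 drives = 9 per scale; 48 × 9 = 432 in all.

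**Men lost if incomplete men are excluded.** Let p be the share of drives without an end rating. The protocol gives no value, so p is assumed. If stops are independent across drives, the expected loss is 48 × [1 − (1 − p)³]. If all stops fall in the same men, it is 48 × p.

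| p | Share lost, independent | Men lost, independent | Men lost, same men |
|---|---|---|---|
| 2% | 5.9% | 2.8 | 1.0 |
| 5% | 14.3% | 6.8 | 2.4 |
| 10% | 27.1% | 13.0 | 4.8 |

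At p = 10% with independent stops, 35.0 men are complete and supply about 314.9 ratings. The ratings never taken number 48 × 3 × 0.10 = 14.4. Ratings collected but discarded are 432 − 314.9 − 14.4 = 102.7, about 103. A model using all available ratings would lose only the 14.

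**Direction of bias (illustration).** A simulation assumed a participant SD of 1, session SD 0.6, residual SD 0.6 and a true end-of-drive benefit of 1 point. A drive stopped when the underlying end score exceeded 9.5, 9.0 or 8.5, with no rating afterwards. Complete men numbered 45.8, 43.2 and 38.9 of 48. The placebo end mean was 7.07, 6.96 and 6.79 against 7.2 in all men. The benefit was estimated as 0.95, 0.92 and 0.88 against 1.0. Every input is assumed.

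**Does changing the model cure it?** In a simulation with all nine ratings, where stopping depended on the unrecorded end score, a mixed model kept every man. It recovered much of the late-night level: placebo end mean 6.86, against 6.65 for complete cases and a true 6.98. The treatment difference hardly moved: 0.91 against 0.90, true value 0.99. Under other assumptions the model change moved the difference from 0.88 to 0.91 and from 0.84 to 0.88. With only end scores in the model it went the wrong way, from 0.91 to 0.86 and from 0.87 to 0.80. The data are then not missing at random, and the model cannot supply the missing score.

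**The case against.** A reader might infer that the plan drops every man without nine ratings and that the sleepiest men therefore leave the results. The protocol does not support that as fact.

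- It nowhere says that incomplete men are excluded. Stata is named only for the line-crossing model, and no procedure is named for the ANOVA. A fit to long-format data would drop only the missing rows.
- A missing and a mistimed end rating are alternatives. A man who stops after the break and is rated at the stop has all his ratings and is kept. His rating may well be high, so mistiming does not clearly remove high scores.
- No stop rate and no breakdown of reasons for stopping are given.
- The simulated bias is small and sensitive to its inputs. Uncapped normal scores can exceed 9, the top of the sleepiness scale. In a version with end scores of 7 under placebo and 6 under treatment, SD 1.5 and correlation 0.5, rounding and capping at 1 to 9 gave a true difference of 0.95 and complete-case estimates of 0.90 and 0.87 at two stopping thresholds.

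All of this stands and limits the claim to what may happen.

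The argument that missing-data rules belong in a statistical analysis plan stands only in part. Whether and when a man is asked for a rating is data collection. If he is not asked at the stop, no later document can recover the answer. The analysis method is also already fixed in the protocol.

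**Conclusion.** The point holds in a limited form. The protocol foresees shortened drives, leaves the remaining ratings undefined, and fixes an analysis that in its usual form needs complete data. Either reading leaves a level of the time factor ill-defined for such drives. Late-night sleepiness and fatigue, and the benefit of the countermeasures on them, may be understated.

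The size is unknown. The range of about 1 to 13 men lost rests on assumed shares of 2% to 10% of drives without an end rating, on the two extreme patterns of stopping, and on exclusion of incomplete men. The direction rests on stopping being related to sleepiness, which is plausible but not documented.

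Only secondary outcomes are concerned. A reader might infer that the line-crossing result is compromised too; nothing in this point touches it. The change should be made because it is cheap and the rating at the stop cannot be recovered later.

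**What to change.** - **Study design, Driving session.** State that sleepiness and fatigue are both rated at the moment any drive stops, with the clock time recorded. This is the essential part: it records the score closest to the stop.
- **Analyses of variables.** For sleepiness and fatigue, replace the repeated-measures ANOVA by a linear mixed model with random effects for participant and for session within participant, using every available rating and session. State how the stop rating enters the model, since filing it at the end level would keep the timing fault.
- **Sensitivity analysis.** Carry the rating at the stop forward to the later planned times.

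The cost is new wording in two sections and one short extra rating in stopped sessions. Sample size, treatment and primary analysis are unchanged. Ratings at later planned times are optional. They should be taken only if they do not delay or interrupt the recorded recovery sleep, because sleep latency, sleep efficiency and slow wave activity are themselves secondary outcomes. Any such rating should be flagged as made at rest rather than at the wheel.

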**Study objectives**

Primary objective

To compare the effects of continuous blue light exposure during driving with those of coffee (2*200 mg of caffeine) and coffee placebo on 4h night-time driving performance in young (20-25 years) and middle-aged (40-50 years) healthy volunteers

Secondary objectives

To determine the effect of age in the effectiveness of countermeasures (blue light and coffee)

To determine individual differences (cognitive, genetic and hormonal) in the impairment of neurobehavioral functions from sleep loss and in the effectiveness of countermeasures (blue light and coffee)

To determine the effects of blue light on quality and quantity of sleep after night-time driving in young and middle-aged healthy volunteers

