**Criteria of assessment**

Primary efficacy criterion

- Number of inappropriate line crossings (ILC) identified from the video recordings.

Secondary efficacy criteria

- Standard deviation of the position of the car
- Self-rated sleepiness during driving
- Self-rated fatigue during driving
- Sleep latency during the subsequent sleep
- Sleep efficiency during the subsequent sleep
- Time course of EEG slow wave activity during the subsequent sleep

Secondary criteria

- Chronotype
- Caffeine sensitivity
- Habitual sleep patterns
- PER3 polymorphism
- COMT polymorphism
- ADORA2A polymorphism
- Reaction time and percentage of errors at cognitive tests
- Saliva cortisol concentration before and after the driving session and after the sleep recovery.
- Saliva amylase concentration before and after the driving session and after the sleep recovery.

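### Cognitive and hormonal markers measured on continuous scales enter the models only as 'types', which loses power for the individual-differences objective; the size of the loss depends on the grouping

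*Protocol*

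**What the plan says.** One of the protocol's secondary objectives is "To determine individual differences (cognitive, genetic and hormonal) in the impairment of neurobehavioral functions from sleep loss" and in the effectiveness of the countermeasures. Expected results lists the characterisation of such markers among the study's products.

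Under Criteria of assessment, the secondary criteria include "Reaction time and percentage of errors at cognitive tests", together with salivary cortisol and amylase concentrations at three times around each drive. All of these are continuous. In Clinical assessment methods, the sub-heading that introduces the genetic and saliva measures describes them as a typing of subjects.

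Under Analyses of variables, the secondary outcomes are analysed by two-way and three-way analyses of variance. For sleepiness, fatigue and the sleep measures the terms include "time*genotype*treatment, time*hormonal type*treatment, time*cognitive type*treatment"; the lateral-position analysis uses the same types crossed with treatment. The primary negative binomial regression lists age or 'type' as determinants without saying which type. The lists of terms in the secondary analyses are left open at the end, but no analysis that keeps a marker continuous is named anywhere.

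**The concern.** In these models the hormonal and cognitive types occupy the same position as genotype and age group, so they act as grouping factors. Genotype is categorical by nature, whereas a reaction time or a cortisol concentration is not. Once it is cut into groups, men on the same side of a cut are treated as alike however far apart they are, and two men on either side of it are treated as different however close they are. The estimated effect then depends partly on where the cut lies.

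The objective at stake is whether these markers explain who is impaired by sleep loss and who responds to light or coffee. The sample size was set for the comparison of countermeasures, so the marker question has no power to spare.

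**Working it through.** **The plan's own figure.** Statistical considerations gives "Effect size f = 0.3", "α err prob = 0.05", "Power (1-β err prob) = 0.9" and "Total sample size: 48". Study design has three conditions: "For each driving session (Blue light, caffeine and placebo of caffeine), all participants will drive 400 km". The G*Power procedure is not named. Noncentral F calculations give:

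- one-way analysis of variance, three groups, f = 0.3: 144 in total, which is 48 per condition, power 0.901;
- repeated measures, one group, three measurements, correlation 0: 49 subjects, with power 0.897 at 48;
- the same with correlation 0.5: 25 subjects.

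So 48 can be reproduced, but it concerns the treatment comparison. The protocol gives no effect size or power for any marker.

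**Information kept after grouping.** Assume a normally distributed marker that acts linearly. The share of linear (r-squared) information kept equals the between-group share of the marker's variance. For two groups cut at quantile p it is φ(z_p)² / [p(1 − p)], which at the median is 2/π = 0.637. The number of groups and the cuts are not stated, so a range is shown.

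| Grouping | Loss |
|---|---|
| Five equal groups | 10% |
| Four equal groups | 14% |
| Three equal groups | 21% |
| Two groups, cut at the median | 36% |
| Two groups, cut at 1/3 | 41% |
| Two groups, cut at 1/4 | 46% |
| Two groups, cut at 1/5 | 51% |

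Skewness shifts these figures. For a log-normal marker with log-SD 0.5 that acts linearly on its raw scale, a median split loses 48%.

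**Effective sample size after a median split.** 48 × 0.637 = 30.6, about 31 men. To make up the loss, 48 / 0.637 = 75.4, so 76 men.

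**Illustrative power, 48 men, two-sided 5%.** By Fisher's z, power = Φ(√45 × atanh(r) − 1.96). A median split multiplies r by √(2/π) = 0.798.

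- r = 0.40: √45 × 0.424 − 1.96 = 0.88, power 81%. After the split r = 0.319: √45 × 0.331 − 1.96 = 0.26, power 60%.
- r = 0.50: power 96%. After the split r = 0.399, power 81%.

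A separate calculation with the noncentral F (1 and 46 degrees of freedom) agrees: 80% falls to 58% at r = 0.38, and 90% to 70% at r = 0.43. If the plan's f = 0.3 is borrowed for a marker, r = 0.3/√1.09 = 0.287, and power falls from 53% to 36%.

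**The case against.** The strongest reply is that the protocol never says that a marker is cut in two, or cut at all. A reader might infer that the plan discards a fixed share of the information, about a third. The documents do not support that: the figure of 36% belongs to a median split of one normal marker, and three or more groups lose less. A cognitive type could also be a profile built across several tests, to which 2/π would not apply. This stands, and it is why the size is given as a range.

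A reader might also infer that the undefined types leave the cut open to choice after the data are seen. That is not supported either. Cut-points are commonly set in a statistical analysis plan, and one may exist here. The point rests only on the form of analysis that the protocol itself fixes: an analysis plan that merely supplied cut-points would still carry the loss.

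The power figures are for a single correlation, whereas the planned tests are interactions of type with treatment, and with time, over three treatments. They are therefore illustrations, not the power of this trial's analyses. Finally, this is a secondary objective for which the trial was not sized, which limits what is at stake.

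What survives is that categorisation is the natural reading of a type used as a factor beside genotype, and that grouping a marker with a smooth effect costs information.

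**Conclusion.** The point holds as a modest improvement to the analysis. The protocol plans continuous cognitive and hormonal markers as type factors, and this costs power on a stated secondary objective with 48 men. The loss is about 36% under a median split and roughly 10% to 50% across the groupings examined.

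These sizes assume a normal marker, a linear effect and one marker grouped at a time. The correlations are assumed as well, since the documents give none. That the types are groupings is a strong inference from the text rather than an explicit statement.

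The point does not extend to every individual difference. Genotype is categorical, caffeine sensitivity is recorded as present or absent, and chronotype is recruited as two separated groups under Selection of participants. The comparison of blue light, coffee and placebo is not affected.

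**What to change.** In Analyses of variables, replace the hormonal and cognitive types by continuous covariates: reaction time, error rate, cortisol and amylase, log-transformed where skewed. Each gets a marker-by-treatment term.

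- For line crossings, the planned negative binomial regression takes these terms as it stands.
- For the secondary outcomes, use a repeated-measures analysis of covariance or a mixed model.
- For cortisol and amylase, use a sample that precedes treatment in the session. Samples taken after driving or after recovery sleep follow treatment, and adjusting for them could remove part of its effect. The first drink is given 30 minutes before the drive, and the protocol does not say whether the pre-drive saliva is taken before it; the wording should settle this.
- Keep age group, genotype, chronotype and caffeine sensitivity as factors.

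The cost is small: a move from plain repeated-measures analysis of variance to a model that takes covariates, and a linearity assumption to check. No additional men or measurements are needed, and groups may still be shown in figures. The change does not by itself deal with the number of cognitive tests examined, which is the same issue under either coding.
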